## 10. Study endpoints

### 10.1 Primary Endpoint

The change in JPAC-QOL from baseline at 2 weeks

### 10.2 Secondary Endpoints

#### 10.2.1 Efficacy endpoints

- Change in SBMs from baseline at 2 and 12 weeks
- Change in JPAC-QOL from baseline at 12 weeks
- Change in PAC-SYM from baseline at 2 and 12 weeks
- Change in CSS from baseline at 2 and 12 weeks
- Change in RomeIV from baseline at 2 and 12 weeks
- Change in BSFS from baseline at 2 and 12 weeks
- Change in SF-36 from baseline at 2 and 12 weeks

#### 10.2.2 Safety endpoint

Incidence of adverse events that occurred from the first day to 28 days after treatment

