**8. Summary of Known and Potential Risks and Benefits in Patients**

8.1 Potential Risks and Benefits in Patients

Taking the study drug may cause occasional or psychological burden. In addition, the study drug may cause side effects due to drug administration. Side effects and adverse events will be appropriately evaluated by medical examination and blood tests at regular visits during the study period. In addition, investigators will make it known to all participants that they can consult with them at any time to promptly respond to any symptoms of side effects that may arise, even outside of the visits specified in the protocol. There is a reasonable possibility that the study drug will provide benefits such as improvement of clinical symptoms and quality of life that have been caused by OIC. There will be no financial benefit from participation in the study.

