8.2 Definitions of Adverse Events

Any unfavorable symptoms or signs (including abnormal laboratory values) occurring within 4 weeks of protocol completion will be reported as an adverse event (AE). AEs may or may not be causally related to the protocol treatment.

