#### 8.4 Expected Adverse Events

The efficacy and safety of the study drugs for patients with OIC or constipation have been confirmed in clinical trials, and the inclusion criteria for suitable patients for administration is established. The study will be conducted with adequate safety monitoring. This is an open-label, randomized controlled trial comparing two groups of study drugs, and there is not enough evidence to show that one is superior to the other. In this study, all medical care during the study period, including study treatment, will be provided as usual medical practice. The medical cost will be covered by insurance. The frequency of visits and examinations in this study will

be the same as in the regular medical practice.

Side effects of the study drugs are as follows.

Magnesium oxide: abdominal pain (1.1%), mild diarrhea (1.1%), mild increase in plasma magnesium levels (9.5%)

Naldemedine: diarrhea (21.9%), abdominal pain (2.2%)

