## 9. Study schedule

### 9.1 Planned Duration of Patient Participation

Protocol treatment period: 12 weeks

Study period: From March 22, 2018 to March 31, 2023

Recruitment period: From March 22, 2018 to March 31, 2021

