## 9.3 Observation, Test and Investigation schedule

|                           | Before enrolment                   | treatment period |   |   |   |    |    |
|---------------------------|------------------------------------|------------------|---|---|---|----|----|
| Week                      | 4weeks before enrolment (baseline) | 2                | 4 | 6 | 8 | 10 | 12 |
| Patients' background      | ⊙                                  |                  |   |   |   |    |    |
| Physical examination      | ⊙                                  | ⊙                | ○ | ○ | ○ | ○  | ⊙  |
| Symptoms (adverse events) | ⊙                                  | ⊙                | ○ | ○ | ○ | ○  | ⊙  |
| JPAC-QOL                  | ⊙                                  | ⊙                |   |   |   |    | ⊙  |
| PAC-SYM                   | ⊙                                  | ⊙                |   |   |   |    | ⊙  |
| CSS                       | ⊙                                  | ⊙                |   |   |   |    | ⊙  |
| RomeIV                    | ⊙                                  | ⊙                |   |   |   |    | ⊙  |

|       |   |   |  |  |  |  |   |
|-------|---|---|--|--|--|--|---|
| BSFS  | ◎ | ◎ |  |  |  |  | ◎ |
| SBMs  | ◎ | ◎ |  |  |  |  | ◎ |
| SF-36 | ◎ | ◎ |  |  |  |  | ◎ |

◎ To be performed

○ When necessary

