### 11.2 Statistics Analysis Plan

The “full analysis set” is defined as any subject who receives any amount of the study medication with initial information on the primary endpoint. The full analysis set will be the primary analysis set for efficacy to use an *intention-to-treat* patient population.

For the primary endpoint, one-way analysis of variance across the 2 groups will be performed with calculating the p-value using the Student’s t-test. The p-value will be significant at a two-sided significant level of 5%. Both the p-value and confidence intervals will be used to determine whether our results are statistically significant or not. The paired t-test or Wilcoxon signed-rank test will be performed to compare before and after the intervention within each group. The chi-squared test will be used to assess the frequency of AE. The treatment compliance rate will be calculated and compared using Fisher’s exact test. The JMP version 11.2.0 software (SAS Institute, Cary, NC, USA) will be used for all statistical analyses.

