## 12. Case Report Forms

Contents: Collection period

Case registration form: at the time of case registration

Start ~ end of protocol treatment: within 14 days after the end of protocol treatment

At the time of discontinuation: within 1 week of visit

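### Adverse events count to 28 days after treatment, but no contact is planned after week 12, and the blood tests promised for safety are missing from the schedule

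*Protocol*

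**What the plan says.** **Window.** Protocol section 10.2.2 defines the safety endpoint as "Incidence of adverse events that occurred from the first day to 28 days after treatment". Read alone, this could mean 28 days from the start of treatment. Section 8.2 points to the post-treatment reading and brings laboratory values into the definition: "Any unfavorable symptoms or signs (including abnormal laboratory values) occurring within 4 weeks of protocol completion will be reported as an adverse event (AE".

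**Contacts.** Section 9.1 gives "Protocol treatment period: 12 weeks". Section 9.2.2 sets visits at 2 weeks (±7 days), at 12 weeks (±14 days) and at discontinuation (up to 2 days later). Section 9.2.3 treats the week 12 visit as the last. In section 9.3 the adverse event row is mandatory at baseline, week 2 and week 12, and is done only when needed at weeks 4 to 10. There is no column after week 12.

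**Forms.** Section 12 names three collection points: registration; "Start ~ end of protocol treatment: within 14 days after the end of protocol treatment"; and, for discontinuation, one week from the visit. Section 8.5.2 has an adverse event form written when an event occurs, with no deadline and no planned contact.

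**Laboratory.** Section 8.1 states: "Side effects and adverse events will be appropriately evaluated by medical examination and blood tests at regular visits during the study period". Section 8.4 lists raised plasma magnesium (9.5%) as the most frequent expected side effect of magnesium oxide. Neither the item lists in 9.2 nor the table in 9.3 contains a laboratory test.

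**The concern.** An incidence needs every patient in the denominator to be asked about the same period. Here the endpoint's period runs past the last planned question by about four weeks, and past the last form deadline by two. An event in that stretch enters the data only if the patient brings it forward and someone opens a separate form. Mild events are the likeliest to be missed.

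The laboratory gap works differently. Raised plasma magnesium is an expected effect of one arm and is seen only in a blood sample. If no analyte or time point is fixed, and clinicians know the allocation, testing may differ by arm. The comparison of adverse event rates would then partly reflect testing practice.

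Both points concern the visit schedule, form timing and endpoint definition. The protocol itself fixes these, so they are not details it would normally leave to a statistical analysis plan.

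**Working it through.** The protocol gives no figure to reproduce, so the check is day arithmetic plus a comparison of sections.

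**1. End of the window.** Treatment is 12 × 7 = 84 days (9.1). The window ends at 84 + 28 = day 112 (8.2, 10.2.2).

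**2. Last planned contact.** The week 12 visit may fall from 84 − 14 = day 70 to 84 + 14 = day 98 (9.2.2). Assuming treatment ends on day 84 whatever the visit date:

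| Week 12 visit | Days to end of window |
|---|---|
| Day 70 | 112 − 70 = 42 |
| Day 84 | 112 − 84 = 28 |
| Day 98 | 112 − 98 = 14 |

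If dosing instead stops at the visit, the gap is 28 days whatever the visit date. For the on-time visit, 28/112 = 25% of the days in the window come after the last contact.

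**3. Form deadlines.**
- Completers: the form is due by 84 + 14 = day 98. Days 99 to 112 lie beyond it, which is 14 of the 28 post-treatment days.
- Discontinuers: the form is due within 7 days of the visit. If the visit is on the stop date, 28 − 7 = 21 days lie beyond the deadline. If it is 2 days later, 28 − 9 = 19 days do.

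**4. Laboratory items.** Side by side:

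| Section | Content |
|---|---|
| 8.1 | Blood tests at regular visits are used to evaluate adverse events |
| 8.2 | Abnormal laboratory values count as adverse events |
| 8.4 | Raised plasma magnesium expected in 9.5% on magnesium oxide |
| 9.2.1 to 9.2.3 | No laboratory item |
| 9.3 | No laboratory row |

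Expected cases on magnesium oxide are 0.095 × 60 = 5.7. The protocol does not give the share of patients who would be tested. Suppose a fraction f of the arm is tested, independently of magnesium level; expected detected cases are then 5.7 × f. That is 5.7 at f = 1, 2.85 at f = 0.5 and 1.4 at f = 0.25. These fractions are illustrative.

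**The case against.** The strongest reply is that late events have a route into the data.
- Section 8.1 lets patients consult at any time outside protocol visits.
- Section 8.5.2 allows an adverse event form whenever an event occurs, with no cut-off.
- Section 8.5.1 has serious events reported immediately.
- Section 7.3 keeps patients who discontinue under criteria (1) to (3) under observation for as long as possible.

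All of this stands. A reader might infer that the forms close at 14 days, or that the incidence cannot be produced. The text supports neither: section 12 sets a collection period for the treatment-period form, and an incidence can still be calculated. But these routes depend on the patient reporting an event. Section 7.3 sets no time point and does not extend its observation to criteria (4) to (6).

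The 25% is also a share of days, not of events, so it does not measure the under-count. Most treatment days lack a mandatory contact too. The post-treatment gap is the same by design in both arms, so it does not by itself favour either.

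On the laboratory point, sections 8.4 and 17.4 say examinations follow ordinary practice. If 8.1 is carried out as written for everyone, the detection problem largely disappears. What remains is that no test, analyte or time is fixed.

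A reader might also object to section 11.2, where "The chi-squared test will be used to assess the frequency of AE", on the ground that chi-squared p-values are too small for rare events. That does not hold here. With 60 per arm and a nominal 5% level, the exact type I error of the uncorrected Pearson test is 0.45% at a common rate of 1.1% and 2.3% at 2.2%, and at most about 5.5% at any common rate from 0.1% to 50%. A split of 4 versus 0 gives p = 0.042 by Pearson and 0.119 by Fisher, but that gap reflects Fisher's conservatism: its type I error at 2.2% is 0.11%. Nor are expected cells always small. For diarrhoea, (0.219 × 60 + 0.011 × 60)/2 = (13.14 + 0.66)/2 = 6.9 per arm.

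**Conclusion.** The concern holds in two parts.

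1. The adverse event window extends 28 days past the last planned contact when the week 12 visit is on time, or 14 to 42 days across the visit window if dosing ends on day 84. At least the last 14 of those days also fall outside every collection point in section 12. Capture there is passive, so the incidence as defined is likely to be under-counted, by an amount the protocol gives no means to estimate. This rests on reading 10.2.2 as 28 days after the end of treatment, which section 8.2 supports.

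2. Section 8.1 and the schedule disagree on blood tests. Up to about 5.7 expected cases of raised plasma magnesium per 60 could be found or missed according to who is tested. Differential detection between arms is possible, not established: it requires that testing is left to practice and varies with known allocation.

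The effect is confined to the safety results. The JPAC-QOL primary endpoint is not touched. The point is worth correcting because the remedy is small.

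**What to change.** **Window.** Choose one of the following:
- Add one telephone adverse event contact at 28 days after the last dose for every patient, including those who discontinue. Show it in 9.3, and set the adverse event form in section 12 to be due after it.
- Restate the window in 8.2 and 10.2.2 so that it ends where active collection ends.

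In either case, word 10.2.2 so that its 28 days clearly run from the end of treatment or are replaced.

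**Laboratory.** Reconcile 8.1 with 9.2 and 9.3. Either enter the blood tests already promised in the schedule, with results recorded at the same times in both arms, or remove the statement that adverse events are evaluated by blood tests and limit the laboratory part of the definition accordingly. The documents do not show which was intended.

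**Cost.** The first window option costs one call per patient (120 at full enrolment) and a later form date. The second costs no resources but gives a shorter stated safety window. Scheduling tests that match usual care costs a table row and data entry. Tests beyond usual care would add expense, which section 17.2 places on health insurance and the participants. No change to the analysis in 11.2 is needed for this point.

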#### 10.2.3 Other endpoints

- Protocol compliance and patients' quality of life will be evaluated using the patient diary.
- Change in JPAC-QOL subscale at 2 and 12 weeks
- Change in JPAC-SYM subscale at 2 and 12 weeks
- Change in complete spontaneous bowel movements (CSBMs)

## 11. Statistical Analysis

### 11.1 Planned Sample Size

Our retrospective analysis of magnesium oxide/naldemedine in 10 OIC patients at

Yokohama City University Hospital showed a mean JPAC-QOL change of -1.19 in the

naldemedine group and -0.76 in the magnesium oxide group. We decided to perform

sample size calculation to attain a relevant number for proper analysis of variance F-test based on these data. Assuming mean changes in the JPAC-QOL score in the naldemedine group and magnesium oxide group to be -1.19 and -0.76, respectively, with a common standard deviation of 0.76, 51 patients are needed in each group to reach 90% statistical power with a two-sided significance level of 5%. To compensate for any dropout, we proposed to increase the sample size to 60 per group. To reach this sample size, a total of 120 patients in the study are needed.

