### **1. Objectives and background of the study**

Opioids are used for cancer pain management [1,2]; however, there are challenges associated with continuous opioid therapy owing to complications such as nausea, constipation, sleepiness, and respiratory depression [3-6]. Constipation develops in 15-64% of patients receiving strong opioid analgesics [7-11]. Long duration of opioid therapy is greatly responsible for opioid-induced constipation (OIC) [12] and drug tolerance against OIC is barely made, so preventive administration of laxatives is important [13].

Over the years, little progress has been made in OIC treatment research [9]. Conventional OIC treatment involves a “non-drug” therapy comprising the consumption of high fiber diets or medications like laxatives, but neither of them targets the underlying mechanism of OIC [3,9]. OIC occurs when opioids act on  $\mu$ -receptors in the intestinal nerves, reducing intestinal motility and intestinal fluid secretion [6,14]. Recently, peripherally acting  $\mu$ -opioid receptor antagonists (PAMORAs), such as naldemedine, were shown to treat OIC. Naldemedine is a novel PAMORA being developed for the treatment of OIC without affecting central analgesia [15] and safety and efficacy of it has been reported to be superior to that of placebos [16,17].

Symptoms brought by constipation (abdominal pain, abdominal fullness, loss of appetite) impairs patients' QOL, hence the need for preventive treatment. This study will compare magnesium oxide to naldemedine and investigate which is more effective in preventing OIC.

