### **5.1 Inclusion Criteria**

1. Patients who received adequate explanation about this study and provided written informed consent
2. Patients who are  $\geq 20$  and  $< 85$  years of age at the time of informed consent
3. Patients who have not started opioid therapy
4. Patients who are scheduled to commence opioid therapy for cancer pain
5. Patients capable of oral intake
6. Patients capable of reporting the patient reported outcomes (PRO)
7. Patients who are prospectively to stay in the stable pathological condition during the observation period

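### The planning difference of 0.43 comes from 10 patients who already had OIC and is unsupported for opioid-naive patients; separately, 51 per arm gives about 81% power on the stated inputs, not 90%

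*Protocol*

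**What the plan says.** Section 11.1 names its source as "Our retrospective analysis of magnesium oxide/naldemedine in 10 OIC patients at" the study hospital and calls the result a "sample size calculation to attain a relevant number for proper analysis of variance F-test based on these data". It then proceeds "Assuming mean changes in the JPAC-QOL score in the naldemedine group and magnesium oxide group to be -1.19 and -0.76, respectively". For the spread of the changes it works "with a common standard deviation of 0.76" and concludes that "51 patients are needed in each group to reach 90% statistical power with a two-sided significance level of 5" per cent. The last step is "To compensate for any dropout, we proposed to increase the sample size to 60 per group", which gives 120 patients in all.

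The trial population is described elsewhere. Inclusion criterion 3 in section 5.1 reads "Patients who have not started opioid therapy", and criterion 4 requires that opioids for cancer pain are planned. Section 1 gives the aim: "This study will compare magnesium oxide to naldemedine and investigate which is more effective in preventing OIC". Section 4 defines OIC as constipation that appears or worsens when opioids are started, changed or increased. Section 9.3 places the baseline assessment before enrolment, and section 10.1 makes the change from that baseline to 2 weeks the primary endpoint.

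**The concern.** The 10 patients had OIC, so their mean changes describe relief of a condition that was already present. Trial participants are measured before any opioid and again 2 weeks into treatment, so the trial measures how far constipation is kept away. The protocol gives no reason why a difference seen in the first setting should carry over to the second. It also names no difference that would be worthwhile in opioid-naive patients.

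Power is what is at stake. If many patients in both arms never become constipated, there is less for either drug to prevent, and the average difference could fall below 0.43. Section 11.2 uses confidence intervals only to decide whether a result is significant, so the plan does not say how a null result from a weaker trial should be read.

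A second problem sits in the same paragraph. The stated number of patients does not give the stated power, even if every planning input is accepted.

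**Working it through.** **Inputs.** From section 11.1: mean changes -1.19 and -0.76, so d = 1.19 - 0.76 = 0.43; SD 0.76; two-sided 5%; 90% power; 51 per arm, raised to 60. From section 6.4: 1:1 allocation. From section 11.2: Student's t-test.

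**Step 1: the plan's own figure.** By the normal approximation, n per arm = 2(z_0.975 + z_power)² × SD²/d², with SD²/d² = 0.5776/0.1849 = 3.124.

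- 90% power: 2 × (1.960 + 1.282)² × 3.124 = 65.7, so 66 per arm. The exact t calculation gives 67.
- 80% power: 2 × (1.960 + 0.842)² × 3.124 = 49.1, so 50 per arm. The exact t calculation gives 51.
- One-sided 5% with 90% power: 54 per arm by the normal approximation, so this does not explain 51 either.

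The stated 51 is therefore the exact-t answer for 80% power. It would fit 90% only with an SD of about 0.66.

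**Step 2: power at the planned sizes.** The noncentrality is d/(SD × √(2/n)).

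- n = 51: 0.43/(0.76 × 0.198) = 2.86; exact power 80.8%.
- n = 60: 0.43/(0.76 × 0.183) = 3.10; exact power 86.7%.

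The step from 51 to 60 fits 15% dropout (51/0.85 = 60). The trial therefore sits between 81% and 87%, depending on how many patients are lost.

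**Step 3: the populations side by side.**

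| | Planning data | Trial |
|---|---|---|
| Patients | with OIC | opioids not yet started |
| OIC at baseline | yes | not possible under the section 4 definition |
| Question | relief of OIC | prevention of OIC |

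**Step 4: how power responds.** These are exact t values at 51/60 per arm. The documents give no JPAC-QOL figures for opioid-naive patients, so the smaller differences and the other SDs are illustrative assumptions.

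| Difference | SD | Power at 51 / 60 |
|---|---|---|
| 0.43 | 0.76 | 81% / 87% |
| 0.3 | 0.76 | 51% / 57% |
| 0.2 | 0.76 | 26% / 30% |
| 0.43 | 0.6 | 95% / 97% |
| 0.43 | 0.9 | 67% / 74% |
| 0.43 | 1.2 | 43% / 49% |

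**Step 5: precision of the planning difference.** Assume a 5 + 5 split (not stated) and that 0.76 is the SD within those patients (also not stated). The 95% interval is then 0.43 ± 2.306 × 0.76 × √(2/5) = 0.43 ± 1.11, or -0.68 to 1.54. A 3 + 7 split widens it to -0.78 to 1.64. On these assumptions, the 10 patients do not fix even the direction of the difference.

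**The case against.** Power depends on the difference between arms and the SD, not on where the two means lie. If the trial's arms changed by 0 and +0.43 instead of -1.19 and -0.76, power would be the same. Improvements of 0.76 to 1.19 may be implausible in opioid-naive patients, but that does not show that 0.43 is wrong. This stands, and it limits the conclusion to unsupported.

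A reader might also infer that participants have no room to improve, or that the trial lists OIC as an exclusion. The text supports neither. Section 5.2 names neither OIC nor constipation in general; OIC is ruled out only by inclusion criterion 3 together with the definition in section 4. Pre-existing constipation is not excluded as such, and section 0.5 plans to assess constipation both before and after drug administration. Some patients may improve, in a proportion the protocol does not give.

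Nor need the error run one way. A smaller SD among unconstipated patients would raise power, as the 0.6 row shows. And although section 11.1 says the calculation is based on the pilot data, it reports only the two means as observed. That the SD comes from those 10 patients is an inference.

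Finally, this is a proof-of-concept phase II trial, where planning from a small pilot is common, and the protocol plans no equivalence conclusion. That excuses a modest sample. It does not excuse printing 90% power that the inputs do not give.

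**Conclusion.** Two separate points hold.

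First, the 0.43 difference is carried over from patients with OIC to a prevention trial without justification, so the power attached to it has no support in the population enrolled. The size of any loss cannot be computed from the protocol; the figures for 0.3 and 0.2 show sensitivity and are not predictions.

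Second, taking 0.43, SD 0.76 and two-sided 5% as given, power is about 81% at 51 per arm and 87% at 60, and 90% needs 67. This rests only on the protocol's own inputs. It would be tempting to blame the pilot population for the fall from 90% to 81%, but that gap is arithmetic and would exist with perfectly relevant planning data.

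The SD of 0.76 has no stated source and repeats the digits of the magnesium oxide mean change. It may be a coincidence or a transcription slip, and the protocol does not allow the two to be told apart.

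**What to change.** Keep 120 patients and revise section 11.1 as follows.

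- Check the SD against its source and state that source. If 0.76 stands, replace the 90% claim with 81% at 51 and 87% at 60 per arm for a difference of 0.43. If another value was meant, recompute with it.
- Say that the difference of 0.43 comes from treated OIC, and stop presenting -1.19 and -0.76 as the expected arm means.
- Add a small table, labelled illustrative, giving power at 51 and 60 per arm for smaller differences (0.3 and 0.2 at SD 0.76) and for a range of SDs.
- State that a non-significant result will be read through the confidence interval for the between-arm difference and not as showing no difference.

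A mid-trial check of the SD is not worth adding: with the number of patients fixed, it would lead to no decision.

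The cost is one paragraph and one table, with no extra patients. The drawback is that the stated power becomes less favourable.

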#### 0.4 Planned number of subjects and study period

Planned number of subjects: 120 subjects (60 for each group)

Study period: From March 22, 2018 to March 31, 2023

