## 6.4 Method of randomization

Eligible patients will be randomly assigned (1:1) to receive 500 mg magnesium oxide thrice daily, or 0.2 mg naldemedine once daily at the central registration center. Randomization will be carried out after the patient has signed the informed consent form. To avoid a large bias, we will stratify age ( $<65$ ,  $\geq 65$ ) and gender (male, female) using computer-generated administered procedure, in permuted-block method.

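### Section 11.1's 51 patients per group give about 81% power on the protocol's own assumptions, not 90%, and the full 60 per group give about 87%

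*Protocol*

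**What the plan says.** Protocol section 11.1 (Planned Sample Size) takes its inputs from a retrospective analysis of 10 patients at the study hospital: "Assuming mean changes in the JPAC-QOL score in the naldemedine group and magnesium oxide group to be -1.19 and -0.76, respectively". Both groups are given the same SD, 0.76. For an analysis-of-variance F-test it concludes that "51 patients are needed in each group to reach 90% statistical power with a two-sided significance level of 5" per cent. It continues: "To compensate for any dropout, we proposed to increase the sample size to 60 per group". No dropout rate is given. Section 0.4 repeats the total of 120, 60 in each group.

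The other design elements that bear on the calculation are also stated. Section 6.4 gives 1:1 allocation. Section 11.2 plans that "one-way analysis of variance across the 2 groups will be performed with calculating the p-value using the Student’s t-test", again two-sided at 5%. Section 11.3 plans no interim analysis, so no alpha is spent early.

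**The concern.** All the inputs to the calculation are printed, and they do not lead to the printed result. A difference of 0.43 against an SD of 0.76 is a standardised effect of about 0.57, and 51 per group is too few to detect that with 90% power at two-sided 5%.

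This calculation is the only justification for the trial size, and it concerns the primary endpoint. Section 8.4 says the evidence does not establish that either drug is superior, so a non-significant result is a real possibility. Readers would judge such a result against a stated 10% chance of missing the assumed difference. If the printed SD is right, that chance is nearly twice as large at the evaluable number the plan expects.

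**Working it through.** **Inputs**

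- Difference in mean change: δ = |-1.19 - (-0.76)| = 0.43 (section 11.1)
- Common SD: σ = 0.76 (section 11.1)
- Two-sided α = 0.05 (sections 11.1 and 11.2)
- Equal groups (section 6.4)
- Unadjusted two-group F-test or t-test (sections 11.1 and 11.2); with two groups F = t², so the power is identical
- Standardised effect: 0.43 / 0.76 = 0.566

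**Attempt to reproduce 51 per group at 90%**

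Normal approximation: n per group = 2 × [σ(z₀.₉₇₅ + z_power) / δ]².

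- 90% power: 2 × [0.76 × (1.960 + 1.282) / 0.43]² = 65.6, so 66
- 80% power: 2 × [0.76 × (1.960 + 0.842) / 0.43]² = 49.04, so 50

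Exact calculation: noncentral t with 2n - 2 degrees of freedom and noncentrality δ / (σ√(2/n)).

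- 90% power: n = 66.6, so 67
- 80% power: n = 50.02, so **51**

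The figure of 51 is therefore not reproduced at 90%. It is reproduced exactly at 80%.

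**Power at the planned sizes**

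| n per group | Noncentrality | Power, exact t/F | Power, normal approximation |
|---|---|---|---|
| 51 | 0.43 / (0.76 × √(2/51)) = 2.857 | 80.8% | 81.5% |
| 60 | 0.43 / (0.76 × √(2/60)) = 3.099 | 86.7% | 87.3% |
| 67 | 0.43 / (0.76 × √(2/67)) = 3.275 | 90.2% | – |

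The type II error at 51 per group is 100 - 80.8 = 19.2%, against a stated 10%.

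**What would reconcile 51 with 90%**

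- With δ = 0.43 kept, the SD would have to be about 0.66 (0.663 gives exactly 90% at 51).
- With σ = 0.76 kept, the difference would have to be about 0.49.

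**Other explanations tried**

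- *Rounding of the inputs.* A favourable reading (δ = 0.44, σ = 0.755) gives 83.0% at 51 and 88.6% at 60.
- *One-sided 5%.* Power at 51 is 88.4%, and 90% needs 55 by the exact method (54 by the normal approximation). The protocol also says two-sided in both places.
- *Dropout allowance.* 51/60 = 0.85, so the increase to 60 implies 15% dropout. That rate is inferred, not stated. Even if nobody dropped out, 60 per group would fall short of 90%.

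**The case against.** The arithmetic is not open to serious dispute, but there are fair objections to how far it reaches.

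- *The document does not show which figure is wrong.* Power, SD, difference and n conflict, and any one of them could be the misprint. If the SD was really 0.66, then 51 per group is correct for 90% and there is no shortfall. This stands, so the consequences described here are conditional on SD 0.76.
- *A copying error in the SD is conjecture.* The printed SD equals the size of the magnesium oxide mean change, which invites the suspicion, but with 10 source patients it could be coincidence. This also stands. It is a question for the sponsor, and the exact match of 51 to 80% power points more towards the power label.
- *The practical shortfall is modest.* At the enrolment target of 60 per group with no dropout, power is about 3 points short; it is about 9 points short only if numbers fall to 51. Type I error is untouched, and this is a single-centre proof-of-concept phase II trial. That is true, but the extra nine patients per group are there to be lost, so 51 is the number on which the power claim rests.
- *Baseline adjustment might recover power.* Section 11.2 plans an unadjusted test, and the protocol gives no correlation between baseline and change. No credit can be taken for adjustment.

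An unseen analysis plan would not help, because the protocol itself makes the numerical statement.

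**Conclusion.** The concern holds. The difference, SD, sample size and power in section 11.1 cannot all be right. Taking the printed difference (0.43), SD (0.76), two-sided 5% level and unadjusted test as given, power is 80.8% with 51 evaluable patients per group and 86.7% with all 60. No number from 51 to 60 per group reaches 90%, which needs 67. With 51 per group and SD 0.76, the difference detectable with 90% power is 0.49, not 0.43.

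These sizes rest on SD 0.76 being the intended value. If the source SD is about 0.66, the power statement is right and the SD is the error. Either way section 11.1 must be corrected, because it is the sole basis for the sample size on the primary endpoint.

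**What to change.** First, check the SD (and the two mean changes) against the retrospective data. Then correct section 11.1 accordingly.

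- *If the SD is 0.76:* state that 51 evaluable patients per group give 80% power (80.8%) for a difference of 0.43 at two-sided 5%, and that 60 per group give 86.7% if none drop out.
- *If the SD is about 0.66:* correct the SD and keep the 90% statement.

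Both are wording changes that keep the 120 patients, the test and the significance level. In the first case the cost is a less favourable stated power.

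If the sponsor wants a true 90% at SD 0.76, the trial needs 67 evaluable patients per group. With the inferred 15% dropout that is 67 / 0.85 = 78.8, so 79 per group and 158 in total, which is 38 more than planned. Section 0.4 would then have to change as well.
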